## Abstract

**Background:**

Atlanto-axial rotatory subluxation (AARS) in pediatric patients is characterized by abnormal or restricted motion between the atlas and axis vertebrae, typically presenting with neck pain, limited mobility, torticollis, and muscle stiffness. Cervical atlanto-occipital joint x-ray in open-mouth position or CT scan reveals an atlanto-occipital distance (AOD) of 2 mm < AOD < 5 mm, or a bilateral atlanto-occipital lateral distance (B-LAD) ≥ 2 mm. Although traditional manipulative and bone-setting techniques in Traditional Chinese Medicine have demonstrated clinical benefits, robust empirical evidence remains limited. Musculoskeletal ultrasound (MUSU), as a modern diagnostic modality, has gained popularity for assessing musculoskeletal disorders.

**Methods:**

This study utilized a randomized controlled trial design, where eligible patients diagnosed with AARS were, randomly assigned (1:1) to either a treatment group (gentle manipulative technique combined with continuous traction) or a control group (traction plus cervical collar immobilization). The treatment group received treatment twice daily, five days per week, for two weeks. The control group received the same traction protocol but wore a neck brace immediately after each traction treatment. The primary outcome measure was musculoskeletal ultrasound (MUSU) findings, while secondary outcomes include Visual Analogue Scale (VAS) pain scores and Neck Disability Index (NDI) scores. Both groups were assessed at baseline, post-treatment, two weeks, and six months after treatment.

**Discussion:**

The primary objective of this study aims to quantitatively assess the efficacy and safety of gentle manipulative therapy combined with continuous traction in pediatric AARS, using MUSU technology.

**Clinical Trial Registration**: http://itmctr.ccebtcm.org.cn/, identifier ITMCTR2025001572.

## Background

Atlanto-axial rotatory subluxation (AARS) in children refers to impaired or fixed motion between the atlas and axis vertebrae of the cervical spine (1), often caused by factors such as upper respiratory infection, cervical inflammation, poor posture, or neck strains (2). Atlanto-axial rotatory subluxation (AARS) typically presents with symptoms like cervical pain, restricted movement, head and neck tilt, and muscle stiffness in the neck muscles (3). Accompanied by torticollis, vertigo, ataxia, and even complications such as stroke (4). Research indicates that AARS is quite relatively common in pediatric populations, accounting for approximately 70% of spinal disorders in children, with the highest rates seen in those under 12 years old, where the incidence is estimated at 68% (5). In contrast, the occurrence of AARS in adults is around 16% (6). If not treated promptly and effectively, the symptoms can persist or recur, negatively impacting the child's physical appearance and quality of life and increasing psychological stress. In severe cases, it may lead to spinal cord compression, which could result in paralysis or other life-threatening conditions. This predicament imposes considerable emotional and financial stresses on families and society at large.

The concept of atlanto-axial rotatory subluxation (AARS) was first introduced by Bell in 1830, yet nearly two centuries later, our understanding of this condition remains insufficient both domestically and internationally (3). The terminology itself is still debated, with synonyms such as Grisel's syndrome, atlantoaxial subluxation, and spontaneous atlanto-axial subluxation being used interchangeably (7). However, most researchers prefer the term “atlanto-axial rotatory subluxation,” which more accurately describes the underlying pathological characteristics and distinguishes the condition from treatments for atlanto-axial dislocation (8). From a Western medical viewpoint, the causes of AARS are seen as complex and varied, with mechanisms that are not fully understood. Some researchers classify the causes into traumatic and non-traumatic categories, while others break them down further into traumatic, spontaneous, congenital, pathological, degenerative, metabolic conditions, and various induced factors (9, 10). In terms of cervical spine biomechanics, changes in cervical curvature have been associated with atlantoaxial instability. From a biomechanical perspective, there are differences between the cervical spine of children and that of adults. The differences are primarily manifest in increased spinal elasticity, greater ligamentous laxity, shallower horizontal articular processes, and the presence of unossified cartilage in children (11). It has been demonstrated that enhanced spinal elasticity in children is associated with increased spinal mobility, but concomitantly reduced stability (12). In addition, heightened ligamentous laxity has been shown to elevate the risk of atlantoaxial joint instability (12). Furthermore, the cartilage in children differs from that in adults in that it has not yet ossified, thereby further increasing the risk of instability and susceptibility to infection. In summary, from a biomechanical perspective, the atlantoaxial joint in children exhibits instability, rendering it more susceptible to subluxation and dislocation. Additionally, some researchers have conducted statistical analyses of clinical data, finding correlations with upper respiratory infections, localized cervical inflammation, and surgical procedures involving the head and neck (13).

Currently, therapeutic approaches for pediatric atlanto-axial rotatory subluxation (AARS) can be broadly divided into two main categories: conservative and surgical interventions (14). Conservative strategies mainly involve the use of non-steroidal anti-inflammatory drugs (NSAIDs), cervical collar traction, and skull traction combined with plaster fixation (15, 16). Surgical options primarily focus on anatomical realignment through atlanto-axial fusion procedures, which include techniques such as Gallie, Harms, and Magerl fusion (17). However, conservative methods like oral medications and traction therapies may have their limitations; including concerns about drug toxicity and the risk of recurrence (18). Furthermore, both conservative and surgical interventions carry the potential for surgical trauma, and may affect the mobility of the cervical spine, potentially leading to various postoperative complications (5).

In Traditional Chinese Medicine (TCM), there is a core belief that muscles should remain flexible, be properly positioned, and respond well to warmth while resisting cold (19). It is thought that muscles flourish in a soft environment and suffer from rigidity; additionally, a good blood supply is vital for muscle health. When blood circulation is smooth, muscle function improves (20). The relationship between muscles and bones is essential. When bones are aligned correctly, muscles can be more flexible. Flexible muscles help maintain bone alignment (21). Muscle contractions and extensions enable bone movements. Bones provide the necessary support for various bodily movements. Ideally, a state of balance, known as “muscle-bone balance,” exists between muscles and bones (22). In children, a condition referred to as AARS is understood as “muscle misalignment and bone misalignment,” which is manifested as reduced muscle flexibility, disordered muscle positioning, and skeletal misalignment (23).

Currently, there are various Traditional Chinese Medicine (TCM) treatment methods available to pediatric atlanto-axial rotatory subluxation (AARS), all of which have been validated through clinical practice. Among these methods, manipulation, bone-setting, and traction are considered the most effective (24, 25). Manipulative techniques work by improving blood circulation in the cervical and shoulder areas through thermal effects, which enhance the elasticity of muscle contractions (26). These techniques also stimulate muscle stretch receptors, making them more sensitive; this indirectly activates the sensory cortex and suppresses the reticular formation in the brainstem. This series of effects leads to reduced local muscle tension and relief from muscle spasms in the cervical and shoulder regions, thereby promoting greater muscular flexibility. Techniques focused on muscle relaxation and restoration can quickly alleviate symptoms such as dizziness, neck pain, and muscle spasms or tenderness that are associated with atlanto-axial joint disorders. TCM bone-setting methods utilize leverage principles, often using the jaw or the side of the head as a pivot point (27). By applying a rotational force known as “inch force”, practitioners can transmit force through the cranio-atlanto-axial joint to realign the axis vertebra, achieving what is referred to as “bone alignment”, which specifically means restoring the proper anatomical position of the vertebra to improve joint function and reduce symptoms. This process effectively minimizes the negative impacts of skeletal misalignment on surrounding tissues, thereby promoting a healing response (28).

The gentle muscle adjustment technique used with continuous traction is based on the idea of balancing attention between muscles and bones, prioritizing muscle relaxation to aid in bone alignment. By applying continuous traction while the patient lies on their back, the therapist can make adjustments to the traction direction based on the child's neck discomfort and tilt. This creates a localized mechanical dynamic condition in the cervical area. This method is specifically designed to accommodate the child's muscle condition, helping to ease discomfort and improve the child's cooperation during treatment, which in turn promotes relaxation. This relaxation helps reduce neck muscle tension, alleviates nerve root compression, and improves symptoms such as neck pain and head tilt. To build on this, gentle muscle techniques are employed. Pressing, kneading, pinching, and rubbing are used to stimulate overactive muscle groups, including the sternocleidomastoid, trapezius, and scalene muscles. These techniques enhance local blood flow and energy circulation, relieve muscle spasms and pain, restore muscle elasticity, and reduce local adhesions, thereby making the muscles more flexible. With this improved muscle flexibility, passive, active, and specific neck movements can be performed, along with engaging in relaxed and pleasant communication with the patient. This allows for effective mechanical traction of the neck and shoulder muscles in a dynamic state, helping to realign misaligned bones and achieve proper bone alignment, ultimately harmonizing the muscular and skeletal components of the atlanto-axial joint.

Currently, therapeutic strategies for pediatric AARS primarily focus on either balancing the treatment of muscles and bones or prioritizing skeletal alignment over muscular interventions. Clinical efficacy assessments largely depend on subjective evaluations or measurements of bone structure. There is a pressing need for thorough investigations into gentle muscle-oriented treatment regimens for pediatric AARS. This highlights the importance of designing methodologically rigorous randomized controlled trials and studies that include objective observational indicators focused on gentle muscle-oriented techniques. Such rigorous research efforts would provide a crucial foundation for standardizing conservative therapeutic approaches for pediatric AARS.

Musculoskeletal ultrasound (MUSU) is an innovative diagnostic technique that offers numerous benefits, such as being cost-effective, user-friendly, quick to perform, and capable of dynamic evaluations (29). It is widely used for diagnosing and screening musculoskeletal disorders (30, 31). One of its advanced applications is real-time shear wave elastography (SWE), a non-invasive imaging method that evaluates the mechanical properties of soft tissues by measuring the transient deformations and displacements caused by ultrasound waves. Shear waves are transverse waves that propagate through tissues, and their speed reflects the tissue's stiffness (32). The elasticity of these tissues indicates their mechanical hardness, and ultrasound elastography provides an objective way to quantify this characteristic, often using parameters like shear modulus or Young's modulus to represent muscle stiffness. There is a direct relationship where increased tissue hardness correlates with faster shear wave propagation, higher Young's modulus values, and reduced tissue elasticity (33). Research has shown a notable increase in the hardness of muscle groups, including the trapezius, scalene, and sternocleidomastoid muscles, in pediatric patients with Adolescent Idiopathic Scoliosis (AARS). This finding underscores the crucial role of MUSU technology in objectively assessing changes in muscle morphology and elasticity in this area of research (34).

This investigation employs a gentle muscle adjustment technique combined with continuous traction as a therapeutic intervention for pediatric patients diagnosed with AARS. A clinical randomized controlled trial design is implemented to assess changes in Visual Analog Scale (VAS) pain scores and Neck Disability Index (NDI) scores, as well as alterations in muscle morphology and elasticity before and after treatment. By quantitatively evaluating the clinical effectiveness of the gentle muscle adjustment technique under continuous traction through MUSU, this study aims to elucidate the specific clinical benefits of this treatment for pediatric AARS. Consequently, it seeks to promote the broader application of this therapeutic approach in the future.

## Methods

### Objective

The objective of this investigation is to clarify the effectiveness and safety of the gentle muscle adjustment technique combined with continuous traction in treating pediatric AARS. We aim to develop a treatment protocol that is not only effective and straightforward but also safe and cost-effective. Furthermore, we will evaluate the role of MUSU technology in assessing changes in neck muscle morphology and elasticity, thereby providing quantitative evidence to support conservative management strategies for pediatric AARS.

### Trial design

This research utilizes a single center randomized, controlled design. Due to the specific nature of the treatment protocols, it is not feasible to blind either the researchers or the participants. Therefore, the study adopts a blind evaluation approach. Under this approach, an independent third-party conducts assessments using various scales, ultrasound examinations, and statistical analyses. This method ensures a clear “three-way separation” among researchers, operators, and randomly assigned in a 1:1 ratio to either a treatment group (gentle muscle adjustment with continuous traction) or a control group (traction combined with cervical-collar fixation for patients with AARS. We expect to randomly assign 70 patients diagnosed with AARS to participate in this study. Randomization will be computer-generated by a statistician independent of the research team. The trial protocol has been registered on the International Traditional Medicine Clinical Trial Registry (http://itmctr.ccebtcm.org.cn/) which is accredited by the World Health Organization as a Level 1 registry, the Clinical trial number: NO. ITMCTR2025001572, the registration date is 19 August 2025, and the report adheres strictly to the guiding principles outlined in the relevant guidelines. Figure 1 provides a flowchart that details the research process. Furthermore, the schedule for the enrollment, treatment and assessment of the trial is show in Figure 2.

**Figure 1 F1:**
[figure not shown]
Flow chart of the study process. AARS, atlanto-axial rotatory subluxation; MUSU, Musculoskeletal ultrasound; VAS, Visual Analog Scale; NDI, Neck Disability Index.

**Figure 2 F2:**
[figure not shown]
Schedule of enrolment, treatments, and assessments. MUSU, Musculoskeletal ultrasound; VAS, Visual Analog Scale; NDI, Neck Disability Index.

### Participants, recruitment, and ethical considerations

The recruitment of participants will be recruited through two main channels: printed recruitment posters within the hospital and online outreach through affiliated networks. During recruitment, potential participants and their guardians will receive detailed information about the inclusion and exclusion criteria, intervention methods, study duration, and potential benefits. After confirming eligibility, informed consent will be obtained from the child's legal guardian. Once consent is documented, participants will be randomly assigned to one of the study groups.

The study protocol has been approved by the Ethics Committee of Hangzhou Traditional Chinese Medicine Hospital, (2024KLL093).

### Diagnostic criteria

The diagnostic criteria for pediatric atlantoaxial rotatory subluxation are established based on the criteria outlined in Xu Shaoting's edition of “Practical Orthopedics”: These criteria include several key components: (1) the patient's history should reveal a recent upper respiratory infection, neck infection, or poor neck posture; (2) clinical symptoms may present as neck pain and neck tilt, with more severe cases which may lead to dizziness and nausea; (3) physical signs can include limitations in cervical movement—particularly restricted flexion, extension, and rotation—accompanied by neck muscle stiffness, asymmetrical muscle development, tenderness at the posterior transverse process of the axis, or visible displacement; and (4) Radiological assessments, such as x-ray or CT demonstrating an atlantodental interval (ADI) falls within the range of 2 mm–5 mm. Additionally, there may be a lateral atlanto-dental interval difference (VBLADS) of 2 mm or greater.

### Inclusion criteria

Participants must meet the following inclusion criteria: (1) fulfillment of the diagnostic criteria for atlantoaxial rotatory subluxation (AARS); (2) age between 6 and 14 years, regardless of sex; (3) voluntary participation with informed consent provided by the child's guardian; and (4) first episode of the condition with no treatment received within the preceding two weeks. All participants must commit to completing the entire two-week treatment protocol and follow-up assessments.

### Exclusion criteria

Participants will be excluded if they meet any of the following criteria: (1) a history of severe trauma resulting in fractures or complete dislocation of the atlanto-axial joint, or congenital abnormalities of the joint; (2) diagnosis of muscular torticollis or any other condition not consistent with the diagnostic criteria for AARS; (3) severe cardiopulmonary disease, history of head or neck surgery, or psychiatric disorders; (4) inability to cooperate with treatment or assessment procedures due to physical or cognitive impairments; or (5) any medical condition rendering participation unsafe or impractical according to the investigator's judgment.

### Randomization and allocation concealment

This investigation strictly follows the framework of randomized controlled trials conducted at a single clinical research facility. A statistician, who is not involved in the study, will use SPSS 22.0 statistical software to generate a sequence of random numbers for the 70 recruited patients, dividing them into two groups: a treatment group that will receive gentle myofascial adjustment therapy and a control group that will undergo traction combined with cervical collar fixation, with each group consisting of 35 participants. The statistician will match the sequence of patient visits to the generated random numbers to finalize the group assignments. These assignments will then be securely stored in opaque envelopes to ensure allocation concealment. During the treatment phase, the physician will access these envelopes in the order of the child's visits to retrieve the group code. The physician will record both the patient code and the group number. Thereafter, after obtaining informed consent and completing the basic information form, the envelopes will be opened in strict numerical order, ensuring that patients receive examinations and treatments as detailed within the envelopes.

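### The randomization section gives two incompatible orders for learning the group and obtaining consent; one contradicts the recruitment section and would break allocation concealment if followed

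*Protocol article*

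**What the plan says.** Two sections of the protocol article deal with the order of consent and allocation.

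Under Participants, recruitment, and ethical considerations, eligibility is confirmed, the guardian consents, and then: "Once consent is documented, participants will be randomly assigned to one of the study groups".

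Under Randomization and allocation concealment, the list is made by someone outside the trial: "A statistician, who is not involved in the study, will use SPSS 22.0 statistical software to generate a sequence of random numbers". The protection is stated as: "These assignments will then be securely stored in opaque envelopes to ensure allocation concealment". Three statements on use follow, in this order:

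- The first is about access. It has a physician go to the envelopes as children attend, in order to learn the group.
- The second is about recording, and the third begins straight after it with consent: "The physician will record both the patient code and the group number. Thereafter, after obtaining informed consent and completing the basic information form".
- The rest of the third statement says that opening takes place at that point, by envelope number.

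The section closes with "ensuring that patients receive examinations and treatments as detailed within the envelopes".

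The Blinding section says that neither participants nor treating clinicians can be blinded. It gives ultrasound, VAS and NDI to an independent evaluator who does not know the groups.

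**The concern.** Read in sequence, the randomization section has the physician obtain the group code and write down the group number, and consent appears only in the sentence after that. The word that opens this sentence places it later in time. The recruitment section requires the reverse.

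This matters more here than in a blinded trial. The clinicians know the arm once treatment starts, so concealment up to enrolment is the main safeguard against selective entry. The blinded evaluator and blinded statistician act after a child is in the trial and cannot correct who was let in.

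The entry criteria also leave room for judgement. A child may be excluded for being unable to cooperate, or because the investigator considers participation unsafe or impractical, and participants must commit to the whole two-week course and follow-up. A physician who already knew the next arm could apply these criteria differently by arm, and a guardian who learned it could decline. Either would make the arms differ at entry in ways that the planned chi-square, rank-sum and t-tests do not address.

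**Working it through.** No arithmetic applies: the point rests on no sample size, power or alpha figure. The check is to set the steps side by side.

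| Step | Recruitment section | Randomization section, first two statements | Randomization section, third statement |
|---|---|---|---|
| Eligibility | Confirmed first | Not mentioned | Not mentioned |
| Guardian consent | Before assignment | Not yet mentioned | Before opening |
| Basic information form | Not mentioned | Not yet mentioned | Before opening |
| Physician obtains the group | After consent | On access to the envelope, by order of visit | On opening, after consent and form |
| Group number recorded | Not mentioned | Before the third statement | Not mentioned |

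1. **Between sections.** The second column and the last column agree that consent comes before assignment. The third column does not: the group is retrieved and recorded before consent is mentioned, and the next sentence is expressly later.

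2. **Within the randomization section.** The assignments are in opaque envelopes. A group number cannot be retrieved and recorded from an envelope that has not been opened. Either the envelope is in effect opened at access, and the later opening means nothing, or it is opened only after consent, and the earlier recording is impossible.

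3. **What triggers access.** Access follows the order in which children visit, not the order in which consented children are enrolled. This also fits allocation ahead of consent, although it does not prove it.

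4. **Who would know.** The text says only that it is the physician, acting in the treatment phase. The treatment sections use the same word for the person who delivers the manipulation. That this person is one of the unblinded treating clinicians is a reasonable inference, but the document does not say so in terms.

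5. **Consequence of each order.** Under the last column concealment is conventional: independent list, opaque envelopes, numerical order, opening after consent. Under the third column the physician knows the arm while consent, and possibly eligibility, is still open. The document does not say which order the site will use.

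**The case against.** The strongest reply is that the third statement settles the matter. It says that the envelopes are opened after consent and the form, in strict numerical order, which agrees with the recruitment section. The two earlier sentences may only outline the procedure, with the last one fixing its timing. The mention of consent dates the opening; it does not strictly say that consent follows the recording. The text is rough in other places too, so one misplaced connecting word is slender evidence of intent.

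Much of this stands. A reader might infer that the plan already defeats concealment. The document does not support that: it contains a correct order alongside an incorrect one, and the list comes from an outside statistician.

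A reader might also infer, from the closing words about examinations set out in the envelopes, that baseline ultrasound, VAS and NDI would be rated by someone who knows the arm. That is not supported either. The Blinding section gives those measurements to an evaluator unaware of the groups, and the closing words do not say which examinations are meant.

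The reply does not remove the contradiction. Staff who follow the section line by line would reach the retrieve-and-record step first. This is also not a detail that an article leaves to the full protocol: the article states the sequence, and states it in two ways.

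**Conclusion.** The point holds as an internal contradiction with a possible serious consequence. The randomization section gives two incompatible orders. One contradicts the recruitment section and, if followed, would reveal the arm to an unblinded physician before consent and final judgement of eligibility, which would break allocation concealment.

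The conclusion rests on two assumptions: that the sentences are read as a sequence in time, as the linking word indicates, and that the physician in question is one of the unblinded treating clinicians.

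No size can be given. The document has no information on how many entry decisions might be affected or how strongly prognosis differs between children, so any figure for the bias would be invented. The case for correction rests on the fact that the analysis cannot reliably repair selection at entry, and that the correction costs almost nothing.

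**What to change.** State one order in the randomization section, in line with the recruitment section:

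1. Eligibility confirmed.
2. Guardian consent signed.
3. Basic information form and baseline assessments completed.
4. Next sequentially numbered opaque envelope opened.
5. Group number recorded against the patient code.

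Delete the two sentences on retrieving the code and recording the group, or move them after the opening. Tie the use of envelopes to the order of enrolled, consented children instead of the order of visits. Naming baseline assessments at step 3 also removes the doubt about which examinations follow opening.

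The cost is a change of wording and a matching instruction to the site. It needs no new data and no change to the sample size or analysis. A separate person to hold the envelopes is not needed to resolve the contradiction.
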